## Abstract

**Introduction:**

Suicide is the fourth leading cause of death in youth. Previous suicide attempts are among the strongest predictors of future suicide re-attempt. However, the lack of data and understanding of suicidal re-attempt behaviors in this population makes suicide risk assessment complex and challenging in clinical practice. The primary objective of this study is to determine the rate of suicide re-attempts in youth admitted to the emergency department after a first suicide attempt. The secondary objectives are to explore the clinical, socio-demographic, and biological risk factors that may be associated with re-attempted suicide in adolescents and young adults.

**Methods:**

We have developed a single-center prospective and naturalistic study that will follow a cohort of 200 young people aged 16 to 25 years admitted for a first suicide attempt to the emergency department of Lyon, France. The primary outcome measure will be the incidence rate of new suicide attempts during 3 months of follow-up. Secondary outcomes to investigate predictors of suicide attempts will include several socio-demographic, clinical and biological assessments: blood and hair cortisol levels, plasma pro- and mature Brain-Derived Neurotrophic Factor (BDNF) isoforms proportion, previous infection with *toxoplasma gondii*, and C-Reactive Protein (CRP), orosomucoid, fibrinogen, interleukin (IL)-6 inflammatory markers.

**Discussion:**

To our knowledge, the present study is the first prospective study specifically designed to assess the risk of re-attempting suicide and to investigate the multidimensional predictive factors associated with re-attempting suicide in youth after a first suicide attempt. The results of this study will provide a unique opportunity to better understand whether youth are an at-risk group for suicide re-attempts, and will help us identify predictive factors of suicide re-attempt risk that could be translated into clinical settings to improve psychiatric care in this population.

**Clinical Trial Registration:**

ClinicalTrials.gov, identifier: NCT03538197, first registered on 05/29/2018. The first patient was enrolled 05/22/2018.

## Introduction

Suicide is a major public health concern, causing more than 700,000 deaths per year worldwide (1). Moreover, as suicidal behaviors prevalence increases during adolescence (2), suicide is reported to be the fourth leading cause of death among people aged 15 to 29 (1). Having a history of suicide attempts is the most important risk factor for suicide, with a recent study reporting a higher risk of suicide mortality for 6 months following a suicide attempt, with a peak mortality risk at 1 month (3). Similarly, the risk of suicide re-attempt is at its highest in the first 6 months after an index attempt, and declines over time (4). The dangerousness of the means and its lethality increase with age (5). With fewer studies focusing on adolescents and young adults, suicide re-attempts are reported to occur in this population in 12% at 3 months (6), 17% at 6 months (7), and in 25–31% at 1 year (8).

The biopsychosocial model of suicide theorizes suicidal behaviors as a result of complex trait and triggering factors including socio-demographic, clinical, and biological determinants (9). Identified individual risk factors for suicide and suicide re-attempts include: a diagnosed psychiatric disease, family history of suicide and psychiatric illness, substance abuse, impulsivity, sexual or physical abuse and bullying, active suicidal ideation, conflicts with romantic relationship, and, most importantly, a personal history of suicide attempt (10).

Regarding the biological underpinnings, most studies conducted in adults have shown that suicidal behaviors could be associated with lower baseline, chronic, and/or reactivity of cortisol levels (11–13), suggesting a failure of the hypothalamo-pituitary-adrenal (HPA) axis stress-response system. Other biological markers of interest involve proinflammatory markers such as C-Reactive Protein (CRP) and interleukin (IL)-6 (14–16), a history of exposure and seropositivity to *toxoplasma gondii* (17), and low levels of Brain-Derived Neurotrophic Factor (BDNF) (18, 19), although the evidence to support their implication is less consistent (20, 21).

These biological processes may be particularly relevant during the transition from adolescence to adulthood, a critical period of development characterized by exposure to interpersonally-themed stressors, increased impulsivity and risk-taking behaviors, and onset of severe psychiatric disorders (22).

Altogether and despite the known burden of youth suicide, this population has been poorly investigated and there is scarce knowledge regarding the potential factors that may differentiate those who will make repeated attempts from those who will not. Therefore, this study is aimed to define the incidence of suicide re-attempt in young first-attempters, and to investigate the association between socio-demographic, clinical, and biological (HPA axis activity with blood and hair cortisol, pro-inflammatory markers with CRP, fibrinogen, orosomucoid and IL-6, infection with *toxoplasma gondii*, and neuroplasticity imbalance measured by the proportion of mature, and pro-BDNF isoforms) variables. Given their specific characteristics, we hypothesize that young first-attempters would be at higher risk of early suicide re-attempt compared to adults.

## Methods

The present prospective cohort SURAYA (SUicide Re Attempts in Young Adults) is currently underway in Lyon (France) and is expected to end in October 2022. The study will involve two investigation centers: recruitment and baseline data collection will take place in the Psychiatric Crisis Unit of Edouard Herriot Hospital (Hospices Civils de Lyon, Lyon, France), and the primary outcome and data at 3 months in the Centre de Prévention du Suicide (*Centre Hospitalier le Vinatier, Bron, France*). The sponsor of the study is the “*Centre Hospitalier le Vinatier*,” Bron, France. The study is conducted in accordance with the recommendations provided in the current version of the Declaration of Helsinki. This study was approved by the local ethics committee (Comité de protection des personnes Sud Méditerranée III—on 01/02/2018) and by the National Agency for the Safety of Medicines and Health Products (ANSM registration number 2017-A03129-44). The study was preregistered in a public database, first registered on 5 May 2018 (https://clinicaltrials.gov registration number: NCT03538197).

### Participants

The inclusion criteria are: (1) be hospitalized for a first suicide attempt in an emergency psychiatric unit, (2) be between 16 and 25 years old, (3) speak fluent French. Participants under curator- or guardianship were not eligible. Interrupted, but not aborted, suicide attempts will also be included. Medical records, when available, will be consulted to avoid errors of inclusion. We will also use the “lifetime suicidal behaviors” section of the C-SSRS to detect false inclusions. All participants will be required to provide written informed consent after a full and fair description of the objectives and needs of the study. Consent for minors will be obtained from the participant and at least from one parent as legal representative.

### Study Design

The overall study design is shown in Figure 1. According to our sample size calculation (see below), 200 adolescents and young adults will be recruited in the study. Upon enrollment, baseline data will be collected. Clinical and socio-demographic data will be investigated through the computerized clinical chart and through relatives if necessary. Psychiatric diagnoses will be established according to the Diagnostic and Statistical Manual of Mental Disorders, Fifth edition (DSM-5) during a standardized psychiatric interview. During hospitalization, participants will complete standardized and validated questionnaires. The morning after admission to the emergency unit, a first blood sample will be taken from fasting patients at 7:00 am for biological measurements. Two other blood samples will be collected and stored at −80°C for future research purposes (one EDTA sample and one PAXgene blood RNA tube). Patients who are not fasting will be rescheduled. All inpatients will benefit from usual psychiatric care and will receive appropriate referrals upon discharge. They will also be integrated into the VigilanS brief contact intervention program (23), which is currently being rolled out nationally, and has demonstrated efficacy in reducing suicide re-attempts (24).

**Figure 1 F1:**
[figure not shown]
Study design. On day 1, first-time suicide attempters aged 16 to 25 will be included in the SURAYA prospective cohort study upon their hospitalization in a psychiatric crisis unit. During their stay, socio-demographic, clinical and biological data will be collected. Three months later, participants will be contacted to retrieve the primary outcome: the presence or absence of a second suicide attempt *(re-attempt)* within the first 3 months. *C-SSRS, Columbia Suicide Severity Rating Scale; CRP, C-Reactive Protein; BDNF, Brain-Derived Neurotrophic Factor; Ig, immunoglobulin; IL-6, interleukin-6; SURAYA, SUicide Re Attempts in Young Adults*.

### Baseline Measures

#### Socio-Demographic Factors

The following information will be collected: age, gender, marital and occupational status, education level, socio-economic status, urbanicity level, migratory status, psychosocial issues (including conflicts with parents, access to healthcare), potential traumatic events, and exposure to suicide in the last 6 months.

#### Psychometric Measures and Clinical Factors

Personal and family medical history, current psychiatric diagnosis and treatments, method of attempted suicide will be collected. Psychometric assessments will be performed using a detailed assessment form containing a battery of validated self-administered questionnaires in their French translation. The following dimensions will be documented: depressive symptoms severity with the Quick Inventory of Depressive Symptomatology (QIDS-SR16) (25), risk for bipolar disorder with the Mood Disorder Questionnaire (MDQ) (26), risk for psychosis with the Prodromal Questionnaire-Brief (PQ-B) (27), hazardous alcohol consumption with the Alcohol Use Disorders Test (AUDIT) (28), nicotine dependence with the Fagerstrom Questionnaire (29), cannabis abuse with the Cannabis Abuse Screening Test (CAST) (30) and the Cannabis Use Disorders Identification Test, revised (CUDIT-R) (31), impulsiveness with Barratt Impulsiveness Scale (BIS-10) (32), anger with the State-Trait Anger Expression Inventory 2 (STAXI-2) (33), childhood traumatic experiences with the Childhood Trauma Questionnaire (CTQ) (34), protective factors against suicidal behaviors with the Reasons For Living (RFL) inventory (35).

Moreover, patients will complete non-validated self-reports: visual analog scales for subjective moral pain, physical pain, suicidal ideation intensity, and a 12-item questionnaire on negative life events during the last 6 months.

The Columbia Suicide Severity Rating Scale (C-SSRS) will be administered by a trained clinician. The C-SSRS is a semi-structured interview with solid psychometric properties designed to assess grading of suicidal ideation and behaviors, validated in various general and clinical populations, including adolescents and adults presenting for psychiatric care (36). In a recent study by Lindh et al. (37), C-SSRS appears to perform well in predicting suicide attempts within 3 months, compared to other suicide risk scales.

#### Biological Factors

The levels of CRP, orosomucoid, fibrinogen, cortisol, IL-6, and anti-toxoplasma gondii immunoglobulin G (IgG) and immunoglobulin M (IgM) will be measured in the blood as routine analyses by the central biological laboratory of the hospital.

To assess a potential imbalance between neurotrophic and proapoptotic systems (38), we will measure the proportion of mature BDNF and pro-BDNF respectively, as exploratory analyses. Plasma mature BDNF and pro-BDNF levels will be assessed by enzyme-linked immunosorbent assay (Biosensis, BEK-2211/2237) in collaboration with biologists from Hospices Civils de Lyon. As a measure of chronic stress exposure in contrast to blood cortisol analysis, we will measure hair cortisol levels. Hair strands will be cut carefully with scissors as close as possible to the scalp, and stored at room temperature in aluminum foil. Cortisol levels will be determined from the 3 cm segment of hair closest to the scalp. This represents hair growth over the 3-month period prior to sampling based on an average hair growth of 1 cm/month. In collaboration with University Hospital of Bordeaux, assays will be performed by Liquid Chromatography with tandem mass spectrometry as previously detailed in the study of Brossaud and colleagues (2021) (39).

### Outcomes

Three months after the initial hospitalization for a first suicide attempt, participants will be contacted by phone to retrieve the primary outcome: the presence or absence of a second suicide attempt *(re-attempt)* within the first 3 months following the first suicide attempt. The data will be collected by a nurse blinded to the patients' initial characteristics, and will be further controlled by 3 independent reviewers to avoid misclassification. Other information regarding recent life events and received care will be gathered. If the patient cannot be reached, their trusted person, previously designated by the patient, will be contacted. In case of no reply, the primary care physician or medical records will be consulted. A suicide attempt is defined as a non-fatal self-directed potentially injurious behavior with the intent to die as a result of the behavior. Secondary outcomes will be baseline socio-demographic, clinical, and biological factors.

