#### Sample Size Calculation

Based on the largest survey study conducted in France by Vuagnat and colleagues (2019) (4), we estimated that 12.4% of the population will be readmitted for suicidal attempt within the 3 months following a first suicide attempt that led to hospitalization. This is also in accordance with the study from Spirito and colleagues (2003) (6) conducted in a comparable sample of youth individuals (12%). Using the Wald Confidence Interval method, we calculated that a sample of 200 participants will be sufficient to reach a precision of +/– 4% calculated as 95 CI = p +/– 1.96 sqrt (p (1–p)/n), with *p* = 0.124.

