#### Primary Outcome

First, the classic incidence rate will be calculated by dividing the total number of new re-attempt cases by the total number of suicide attempters. Next, the person-time incidence rate will be calculated by dividing the total number of new re-attempt cases by the sum of the person-time of attempters. This proportion will be compared to the estimated 12.4% based on the literature.

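### The re-attempt event is restricted to non-fatal acts, so by implication a suicide death within 3 months counts as no re-attempt

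*Protocol article*

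**What the plan says.** All references are to the protocol article.

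- **Event definition (Outcomes):** "A suicide attempt is defined as a non-fatal self-directed potentially injurious behavior with the intent to die as a result of the behavior".
- **Primary outcome (Outcomes):** "the presence or absence of a second suicide attempt" in the 3 months after the index attempt. The abstract words it as a rate: "The primary outcome measure will be the incidence rate of new suicide attempts during 3 months of follow-up".
- **Estimators (Primary Outcome):** a proportion, obtained by "dividing the total number of new re-attempt cases by the total number of suicide attempters", and a person-time rate, obtained by "dividing the total number of new re-attempt cases by the sum of the person-time of attempters". The result is then compared with 12.4%.
- **Risk factors (Secondary Outcomes):** participants with and without a re-attempt are compared variable by variable. Variables with a P-value under 0.2 go into a multiple Cox model.
- **Benchmark (Sample Size Calculation):** "we estimated that 12.4% of the population will be readmitted for suicidal attempt within the 3 months following a first suicide attempt".
- **Timing of suicide deaths (Introduction):** suicide mortality is raised for 6 months after an attempt, "with a peak mortality risk at 1 month".
- **Index attempts (Participants):** "Interrupted, but not aborted, suicide attempts will also be included".

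Nothing in the article adds suicide death to the primary event, makes it a separate outcome, or says how it enters any of the analyses. The planned handling of missing data, mentioned in the Discussion, applies when no information can be obtained.

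**The concern.** A suicide death soon after the index attempt is the most severe form of the event under study, and the Introduction places the peak of suicide mortality inside the follow-up window. Yet the event definition excludes it. This is a restriction written into the primary outcome, not a detail left for a fuller document. An analysis plan that counted suicide deaths as re-attempts would contradict the Outcomes section as it stands.

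Two things are at stake. The reported 3-month rate would leave out the fatal re-attempts. The predictor analysis would place participants with the worst outcome among those without a re-attempt. In the Cox model, the best available treatment under this definition is censoring at death. The model then describes non-fatal re-attempts only. Reading its hazard ratios as predictors of re-attempt in general would require that those who died by suicide had the same re-attempt risk as those still under observation, which is not plausible.

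A smaller question concerns interrupted attempts. They qualify a person for entry, but the follow-up definition asks for potentially injurious behaviour and does not mention them.

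**Working it through.** **1. How a suicide death is classified.** Take a participant who dies by suicide in month 1 with no earlier non-fatal re-attempt.

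| Step | Text used | Result |
|---|---|---|
| Is the act a suicide attempt? | Outcomes: must be non-fatal | No |
| Is the primary outcome present? | Outcomes: presence or absence of a second attempt | Absent |
| In the denominator? | Primary Outcome: all attempters | Yes |
| In the numerator? | Primary Outcome: re-attempt cases | No |
| Group in the univariate tests | Secondary Outcomes: re-attempt or none | None |
| Cox model | Secondary Outcomes: no rule for death | At best censored at death |

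The missing-data provision does not change this. Where the participant cannot be reached, the trusted person is contacted, then the primary care physician or the medical records. A death learned of in this way is known information. A participant who had a non-fatal re-attempt before dying is still counted.

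**2. Yardstick: the plan's own precision.** Inputs from Sample Size Calculation: p = 0.124, n = 200.

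1.96 × √(0.124 × 0.876 / 200) = 0.0457, or 4.6 percentage points.

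The article states 4 points. That discrepancy is a separate matter and does not bear on this point. The value of 4.6 is used here only for scale.

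**3. Effect per death.**

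- Change in the proportion: 1 / 200 = 0.5 percentage points.
- Expected events: 200 × 0.124 = 24.8, so one death is 1 / 24.8 = 4.0% of them.
- Share of the half-width: 0.5 / 4.57 = 11%.

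**4. Range.** The article gives no suicide-death rate, so 0 to 4 deaths in 200 (0 to 2%) is an assumption. The number of non-fatal re-attempters is set at 25. With d deaths, the written definition gives 25/200, counting the deaths gives (25 + d)/200, and the share of all fatal plus non-fatal events that is missed is d/(25 + d). The last column shows what would happen if the deaths were dropped as missing, 25/(200 − d).

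| Deaths d | As written | Deaths counted | Share of events missed | Deaths dropped |
|---|---|---|---|---|
| 0 | 12.5% | 12.5% | 0% | 12.5% |
| 1 | 12.5% | 13.0% | 3.8% | 12.6% |
| 2 | 12.5% | 13.5% | 7.4% | 12.6% |
| 3 | 12.5% | 14.0% | 10.7% | 12.7% |
| 4 | 12.5% | 14.5% | 13.8% | 12.8% |

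For the shift to equal the half-width would take 4.57 / 0.5, or about nine deaths, which is 4.5% of the cohort.

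**The case against.** The strongest reply is that the definition fits the stated aim. The study sets out to measure re-attempts, and the Introduction treats suicide mortality and re-attempt as separate quantities. The 12.4% comparator is readmission for an attempt, which by its wording is a non-fatal outcome. Replacing the primary event with a fatal-or-non-fatal one would take the comparison off that benchmark. This stands, and it is why the non-fatal rate has to be kept and used for the comparison. It does not justify leaving the deaths in the group without a re-attempt.

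A second reply is that redefining the primary event is more than wording, because Trial Status already reports a re-attempt rate of 17.81% in the first 73 patients (13/73). This stands too, as a reason to date the change and report both rates.

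Four stronger readings might be inferred, and the documents do not support them:

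- **That the plan expressly scores a suicide death as no re-attempt.** It does not. This follows from the definition and the denominator taken together.
- **That the primary rate is materially biased.** No death rate is given. The remark on the peak at 1 month concerns timing, not frequency.
- **That risk-factor associations are pulled towards the null.** This would depend on fatal and non-fatal acts sharing predictors, which the documents do not show.
- **That interrupted re-attempts are excluded at follow-up.** The definition covers suicide attempts in general and nothing rules them out. Whether an interrupted act is potentially injurious is a matter of reading, and three independent reviewers check the classification.

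**Conclusion.** The concern holds as an implication of the written definition. A participant known to have died by suicide within 3 months, without an earlier non-fatal re-attempt, is a non-event in the proportion and in the group comparisons, and at best informatively censored in the Cox model. No other section corrects this.

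The numerical effect is certain only per death. The total depends on a number of deaths that the article does not supply. It is zero if none occur and, under the assumed 1 to 4 deaths, 0.5 to 2.0 points, which is below the 4.6-point half-width. The reason to act is that the worst outcomes are placed in the wrong group at the primary endpoint and the repair is cheap. The point on interrupted attempts is only an ambiguity to clear up.

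**What to change.** 1. Count suicide death within 3 months as an event on its date, so that the event reads as fatal or non-fatal re-attempt. Apply this in the incidence estimates, the risk-factor comparisons and the Cox model.
2. Treat death from other causes as censoring or as a competing event, and say which.
3. Also report the non-fatal rate, and use it for the comparison with the 12.4% readmission benchmark.
4. Date the change, state that it follows the preliminary analysis of 73 patients, and show both rates.
5. Confirm in one sentence that interrupted attempts are classified the same way at follow-up as at entry.

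The cost is an amendment to the outcome wording and one additional reported rate. The contacts and records already used to retrieve the outcome can reveal deaths, so no new data collection is needed. The small downside is that the event is broadened after some outcome data have been seen, which items 3 and 4 make visible to the reader.

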### Statistical Analysis

Statistical analysis will be performed using R software version 4.02. The significance level alpha will be set at 0.05, and all statistical tests will be 2-tailed.

